## 6. INFORMED CONSENT

Informed consent will be obtained in accordance with the Declaration of Helsinki, ICH GCP, US code of federal regulations for protection of human subjects (21 cfr 50.25[a,b], cfr 50.27, and cfr part 56, subpart a), the health insurance portability and accountability act (HIPAA), and local regulations at USC and USC Norris.

See **Appendix 6** for the informed consent form we propose to use for the prospective clinical trial participants who we engage in response to the social media intervention via Twitter. We will apply for a waiver of written consent. A properly executed, oral, informed consent will be obtained from each Twitter user who prior to entering his/her data into this trial. Twitter users will be interviewed by one of the USC Norris disease experts. Information will be given in both oral and written form (via email if provided) and participants will be given ample opportunity to inquire about details of the study.

## 7. CONFLICT OF INTEREST

[name] and [name] from the private-sector partner Symplur will serve as consultants on the project. We have involved the USC Office of Compliance to manage the conflict of interest (COI) from our private-sector partners in close. USC complies with the PHS regulations on Responsibility of Applicants for Promoting Objectivity in Research for which PHS Funding is Sought (42 C.F.R. Part 50, Subpart F). All disclosed conflicts will be reviewed by USC's COI Review Committee (CIRC) and either eliminated or managed prior to commencing research. [name] and [name] will not be involved in the data collection, analysis and interpretation. The study PI's, co-investigators and expert consultants don't report any COI at this point in time. Additionally, the project team will fully disclose any conflicts in presentations and publications.

## APPENDIX 1: FULL TWITTER USER DATA ANALYSIS BY CANCER DISEASE TYPE IN CALIFORNIA

English Twitter messages, Analysis period: Jan 1, 2016 - Jan 30, 2017

| Disease              | Users  | Tweets | Source: Symplur Signals                                                                         |
|----------------------|--------|--------|-------------------------------------------------------------------------------------------------|
| Breast Cancer        | 14,782 | 76,952 | https://signals.symplur.com/r/608dc26cdd |
| Leukemia             | 2,645  | 13,166 | https://signals.symplur.com/r/5d7c16e238 |
| Lung Cancer          | 3,107  | 16,106 | https://signals.symplur.com/r/c816c460c1 |
| Pancreatic Cancer    | 1,269  | 5,345  | https://signals.symplur.com/r/3a15039a1a |
| Brain Cancer         | 1,741  | 4,365  | https://signals.symplur.com/r/e2b3f1bb35 |
| Sarcoma              | 257    | 431    | https://signals.symplur.com/r/5d64e7caac |
| Kidney Cancer        | 690    | 1,850  | https://signals.symplur.com/r/9d4aa2b40a |
| Colon Cancer         | 1,882  | 5,585  | https://signals.symplur.com/r/e07fac2dcd |
| Head & Neck Cancer   | 102    | 398    | https://signals.symplur.com/r/249ec3b4f2 |
| Gynecological Cancer | 191    | 1,124  | https://signals.symplur.com/r/4881c25b33 |
| Prostate Cancer      | 4,610  | 12,950 | https://signals.symplur.com/r/20c3f0ca66 |
| Skin Cancer          | 2,298  | 8,108  | https://signals.symplur.com/r/f913742b24 |
| Liver Cancer         | 194    | 315    | https://signals.symplur.com/r/f33ba92527 |
| Bladder Cancer       | 306    | 751    | https://signals.symplur.com/r/52bb7efe93 |
| Lymphoma             | 1,445  | 8,711  | https://signals.symplur.com/r/f986385f5b |
| Myeloma              | 983    | 3,239  | https://signals.symplur.com/r/b04cc2742f |

## APPENDIX 2: ACCRUALS and ACCRUAL TARGETS BY TUMOR TYPE

Lung, Colon, Breast, Prostate, Kidney and Lymphoma

| Patient Accrual Diagnosis Site: Lung             |      |      |      |      |      |      |
|--------------------------------------------------|------|------|------|------|------|------|
| Trial Category                                   | 2017 | 2016 | 2015 | 2014 | 2013 | 2012 |
| Interventional Therapeutic                       | 17   | 33   | 34   | 19   | 16   | 32   |
| Interventional (Therapeutic and Non-Therapeutic) | 19   | 37   | 34   | 19   | 16   | 32   |

\*2017 accruals are from 1/1/2017 to 06/27/2017.

| Patient Accrual Diagnosis Site: Colon            |      |      |      |      |      |      |
|--------------------------------------------------|------|------|------|------|------|------|
| Trial Category                                   | 2017 | 2016 | 2015 | 2014 | 2013 | 2012 |
| Interventional Therapeutic                       | 21   | 49   | 83   | 81   | 45   | 47   |
| Interventional (Therapeutic and Non-Therapeutic) | 21   | 49   | 83   | 81   | 46   | 47   |

\*2017 accruals are from 1/1/2017 to 06/27/2017.

| Patient Accrual Diagnosis Site: Breast           |      |      |      |      |      |      |
|--------------------------------------------------|------|------|------|------|------|------|
| Trial Category                                   | 2017 | 2016 | 2015 | 2014 | 2013 | 2012 |
| Interventional Therapeutic                       | 33   | 64   | 63   | 79   | 104  | 151  |
| Interventional (Therapeutic and Non-Therapeutic) | 35   | 75   | 117  | 167  | 162  | 211  |

\*2017 accruals are from 1/1/2017 to 06/27/2017.

| Patient Accrual Diagnosis Site: Prostate         |      |      |      |      |      |      |
|--------------------------------------------------|------|------|------|------|------|------|
| Trial Category                                   | 2017 | 2016 | 2015 | 2014 | 2013 | 2012 |
| Interventional Therapeutic                       | 21   | 52   | 68   | 69   | 68   | 58   |
| Interventional (Therapeutic and Non-Therapeutic) | 23   | 52   | 68   | 71   | 68   | 79   |

\*2017 accruals are from 1/1/2017 to 06/27/2017.

| Patient Accrual Diagnosis Site: Kidney           |      |      |      |      |      |      |
|--------------------------------------------------|------|------|------|------|------|------|
| Trial Category                                   | 2017 | 2016 | 2015 | 2014 | 2013 | 2012 |
| Interventional Therapeutic                       | 4    | 7    | 27   | 49   | 36   | 30   |
| Interventional (Therapeutic and Non-Therapeutic) | 4    | 7    | 27   | 49   | 36   | 30   |

\*2017 accruals are from 1/1/2017 to 06/27/2017.

| Patient Accrual Diagnosis Site: Lymphoma         |      |      |      |      |      |      |
|--------------------------------------------------|------|------|------|------|------|------|
| Trial Category                                   | 2017 | 2016 | 2015 | 2014 | 2013 | 2012 |
| Interventional Therapeutic                       | 4    | 9    | 7    | 8    | 11   | 12   |
| Interventional (Therapeutic and Non-Therapeutic) | 4    | 9    | 7    | 8    | 11   | 12   |

\*2017 accruals are from 1/1/2017 to 06/27/2017.

## APPENDIX 3: Overview of Twitter Outreach Message Templates

### Twitter recruitment message templates we propose to use for contacting those Twitter users in LA County

*(i.e., those who mentioned one of the select disease categories lung cancer, colon cancer, breast cancer, prostate cancer, kidney cancer and lymphoma in the past 6 months or during the research study period)*

*Abbreviation: URL = Uniform Resource Identifier is the global address of documents and other resources on the World Wide Web. The URL to the respective trial group will be included in each Twitter recruitment message. For example, a message about open lung cancer trials at USC Norris will link to the web page that lists all lung cancer trials.*

*#disease will be replaced by the respective disease.*

#### INITIAL CONTACT

Dear @JaneDoe or Hi @JaneDoe or Hello @JaneDoe,

- We noticed your interest in #disease and wanted to share the latest open clinical research opportunities @KeckMedUSC. You can find more information here: URL #ClinicalTrial
- We noticed your mention of #disease and wanted to reach out. Did you know about these open #disease studies @KeckMedUSC? You can find more information here: URL #ClinicalTrial
- We noticed your interest in #disease and wanted to share the latest open clinical research opportunities @KeckMedUSC. You can find more information here: URL #ClinicalTrial
- We noticed your interest in #disease and wanted to share that the following #disease clinical trials @KeckMedUSC are looking for participants. More information is available here: URL #ClinicalTrial
- We noticed your interest in #disease and thought you might be interested in open #disease clinical trials @KeckMedUSC that are looking for participants. More information is available here: URL #ClinicalTrial

#### FOLLOW-UP IF NO RESPONSE AFTER INITIAL CONTACT

*If a prospective participant does not respond, we will send a one-time follow-up message within two weeks of initial contacting.*

Dear @JaneDoe or Hi @JaneDoe,

- Let us know if you have any questions about open #disease trials @KeckMedUSC. We'd be happy to help. Feel free to send us a direct message.

- We're following up on our previous message about clinical trials @KeckMedUSC. Feel free to contact us via DM if you have any questions. We'd be happy to help.
- Let us know via direct message if you have any questions about #disease trials @KeckMedUSC. We'd be happy to help.
- Did you have any questions about ongoing #disease trials @KeckMedUSC? Let us know. Feel free to contact us via DM. We'd be happy to help.

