| Kidney cancer              | #KidneyCancer
kidney [AND] cancer                                                          |
| Lymphoma                   | #Lymphoma                                                                                     |
| Non-small cell lung cancer | #LCSM (lung cancer and social media)
#LungCancer
lung [AND] cancer [AND] non-small cell |
| Prostate cancer            | #PCSM (prostate cancer and social media)
#ProstateCancer
prostate [AND] cancer          |

We will send identified Twitter users IRB-approved messages via the Twitter account we create for the purpose of this project @USCNorrisTrials to attract their attention, engage, and recruit them into the enrolled clinical trials. Message example: @JaneDoeA, this may be of interest to you. Researchers @USC are looking for participants for this new #LungCancer trial [Link to clinical trial webpage]. See **Appendix 3** for overview of Twitter outreach message templates.

Outgoing messages will be public and organic (not advertised). Twitter does not permit paid advertisement for clinical trials. The messages will refer recipients to the respective cancer disease trial group webpage hosted by the USC Clinical Studies Directory. For example, a message may promote lung cancer trials at USC Norris and refer Twitter users to the webpage that lists all recruiting lung cancer trials at USC Norris. An easy-to-use contact form that asks for the name and email can be used by the user to contact the study team. See **Appendix 4** shows an example of such a webpage. The web page content used for this research will be submitted to the IRB once we enroll the trials and know their focus and consent information. The consent information will guide the content we use on the web pages.

Using the contact form on the web page will trigger an email to the SC CTSI study team ([name], [name]) who will then triage the request to the respective cancer disease contact at USC Norris. See also Figure 1. For the purpose of tracking, we will tag each message through an element descriptor in the Hypertext Markup Language. This will allow us to determine the recruitment results by individual and message.

There is no active control group in this study. Success will be compared to historical success achieved without the use of SML at USC Norris for trials in the selected disease cancer categories.

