|--------------------------------------|----------------------------------------------------------------------------------------------------------------------------------------------------------------------------------------------------------------------------------------------------------------------------------------------------------------------------------------------------------------------------------------------------------------------------------------------------------------------------------------------------------------|
| trial participants                   | who spoke with the study team)                                                                                                                                                                                                                                                                                                                                                                                                                                                                                 |
| Diversity of enrolled participants   | Number of people of a specific racial/ethnic background enrolled per month/number of all people enrolled per month                                                                                                                                                                                                                                                                                                                                                                                             |
| Message click rate                   | Number of times a message link was clicked/Number of message impressions                                                                                                                                                                                                                                                                                                                                                                                                                                       |

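### The four follow-up templates carry no link, which contradicts the protocol's own URL and tagging rules and leaves the denominator of the primary click rate unclear

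*Protocol*

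**What the plan says.** Appendix 3 sets out two recruitment contacts. The five initial templates all give the disease-page link, in the form "You can find more information here: URL #ClinicalTrial" or close to it. For the second contact the rule is "If a prospective participant does not respond, we will send a one-time follow-up message within two weeks of initial contacting". The four follow-up templates contain no URL, and each asks the user to reply by direct message, for example "We're following up on our previous message about clinical trials @KeckMedUSC. Feel free to contact us via DM if you have any questions".

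The introduction to Appendix 3, under the heading that covers both sets of templates, states "The URL to the respective trial group will be included in each Twitter recruitment message".

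Section 3.3.4 (Study intervention) says that for tracking "we will tag each message through an element descriptor in the Hypertext Markup Language", with the purpose "This will allow us to determine the recruitment results by individual and message". It describes intake through the web contact form, which triggers an email that is then triaged. It describes no direct-message route.

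Table 3 in section 3.3.7 defines the message click rate as "Number of times a message link was clicked/Number of message impressions". The synopsis lists this rate among the primary outcomes. Appendix 5 records clicks and impressions per message, both at one week. It has no variable that separates initial from follow-up messages and none for a direct-message response.

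**The concern.** The protocol states one rule about links and then gives templates that break it. Two things depend on which is followed.

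The first is attribution. The tag can report results by message only if the message has a link to be followed. The follow-up goes to every non-responder and so may be a large share of all messages sent. Sent as drafted, it falls outside the tracking plan.

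The second is the click rate. A message without a link can add impressions but no clicks. Table 3 does not say whether such messages count, so two analysts could compute different rates from the same data.

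The pilot is meant to support a larger grant proposal, and these rates are part of what it will carry forward. A click rate that mixes messages that can be clicked with messages that cannot would understate the yield of a linked message. The contribution of the second contact would also be hard to separate from that of the first.

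**Working it through.** **Consistency check**

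| Item | Where | Content |
|---|---|---|
| Rule on links | Appendix 3, introduction | URL in each recruitment message |
| Initial templates | Appendix 3 | 5 of 5 carry a URL |
| Follow-up templates | Appendix 3 | 0 of 4 carry a URL; 4 of 4 invite a direct message |
| Tagging | 3.3.4 | Each message tagged, to give results by individual and message |
| Click rate | Table 3 | Link clicks over impressions; message type not restricted |
| Message variables | Appendix 5 | Clicks, impressions, replies, shares, likes; no initial/follow-up flag; no direct-message variable |
| Contact variables | Appendix 5 | Message content and date, acknowledgement and its date, eligibility, enrolment |

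The rule and the follow-up templates cannot both be followed as written.

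**Effect on the click rate if follow-ups are counted**

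The protocol states no click rate, response rate or impression count, so there is no planned figure to reproduce. Let:

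- N = users sent an initial message
- i = impressions per initial message
- c = clicks per impression for initial messages
- f = share of users sent a follow-up (not given; assumed 0.5 to 1.0)
- m = impressions per follow-up divided by impressions per initial message (not given; assumed 0.25 to 2)
- clicks on a follow-up = 0, because it has no link

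Initial messages only: rate = c·N·i / (N·i) = c.

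Both messages: rate = c·N·i / (N·i + f·N·m·i) = c / (1 + f·m).

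Pooled rate as a fraction of the initial-only rate = 1/(1 + f·m):

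| f | m = 0.25 | m = 0.5 | m = 1 | m = 2 |
|---|---|---|---|---|
| 0.5 | 0.889 | 0.800 | 0.667 | 0.500 |
| 0.8 | 0.833 | 0.714 | 0.556 | 0.385 |
| 0.9 | 0.816 | 0.690 | 0.526 | 0.357 |
| 1.0 | 0.800 | 0.667 | 0.500 | 0.333 |

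For example, f = 0.8 and m = 1 give 1/1.8 = 0.556; f = 1.0 and m = 2 give 1/3 = 0.333; f = 0.5 and m = 0.25 give 1/1.125 = 0.889. Over the whole assumed range the reduction is 11% to 67%. If the denominator is restricted to messages with a link, the factor is 1.00.

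**What can still be tracked**

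The acknowledgement flag in Appendix 5 is not tied to a channel, so a direct-message reply can be entered there. Its date can be compared with the dates of the contact messages, and replies and likes are held per message. A response after the follow-up can therefore be partly reconstructed. Three gaps remain:

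- The follow-up has no link-based attribution.
- Message content and date are each listed once among the contact variables, with no statement that they repeat for each message sent.
- Someone prompted by the follow-up to return to the first link is credited to the initial message or, if the follow-up goes out after day 7, may fall outside the one-week click count.

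**The case against.** The strongest reply is that the protocol never says follow-ups enter the click rate. A definition built on clicks on a message link can be read as covering only messages that have one. Message content is recorded, so messages without a link could be filtered out at analysis, and a SAP that is not shown here may settle the denominator. If the appendix's own rule governs, the templates merely lack a placeholder and no unclickable message is ever sent. This stands in part: pooling is a possible reading, not a stated plan. It does not remove the contradiction between the rule and the templates, and a later analysis plan cannot restore a link or a tag that was never sent.

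Three stronger readings are tempting, and the documents support none of them:

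- **That the click rate is halved.** This needs follow-ups to be pooled, at least about 80% of users to receive one, and a follow-up to draw about as many impressions as an initial message. The protocol gives none of these.
- **That the follow-up cannot be tracked.** The acknowledgement, date and reply fields allow partial reconstruction. Section 3.3.5 also has the team track each contacted user's online engagement, and the Appendix 6 questionnaire asks for the Twitter handle, although this may be declined.
- **That the contact-form usage rate is biased.** Table 3 defines it per webpage session. A person who replies by direct message without opening the page enters neither numerator nor denominator.

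It is also fair to say that inviting questions by direct message is a legitimate way to engage people, and that the click rate is one of many descriptive measures with no success threshold attached. Both points limit the weight of the finding.

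**Conclusion.** The point holds as an internal contradiction with a measurable consequence. The four follow-up templates break the rule that each recruitment message carries the URL, and they leave nothing for the tagging plan in section 3.3.4 to record. Direct-message responses have no field of their own.

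For the click rate, the direction is certain if follow-ups are counted: it can only fall. The size is not known. It is 0.50 to 0.56 of the initial-only rate if f is 0.8 to 1.0 and m = 1, and 0.33 to 0.89 over f of 0.5 to 1.0 and m of 0.25 to 2. All of these ranges are assumptions. If follow-ups are excluded, or carry no-one's impressions into the denominator, this dilution does not arise.

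The change should be made before launch, because missing links and flags are hard to recover afterwards.

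**What to change.** 1. Add the tagged disease-page URL to all four follow-up templates, as the introduction to Appendix 3 already requires. The direct-message invitation can stay.
2. In Table 3, restrict the click-rate denominator to impressions of messages that contain a link, and report initial and follow-up messages separately.
3. Add two fields to Appendix 5: message type (initial, follow-up, information) and response route (form, direct message, phone).

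The cost is slightly longer follow-up messages, IRB review of the revised wording, and two extra data fields.

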### **Twitter message templates we propose to use to manage data security and privacy issues**

Dear @JaneDoe: To protect your privacy, we suggest you delete your message. Please contact us directly URL

Hi @JaneDoe: The security of social media is not guaranteed. Contact us about the study. Don't post if concerned about privacy.

### **Message templates to convey general information about participating in clinical trials and this particular project**

*The following content is based on educational information developed by the National Institutes of Health (NIH) for the initiative "NIH clinical research trials and you" (<https://www.nih.gov/health-information/nih-clinical-research-trials-you>)*

*Note: Study team members [name] and [name] will take any resulting phone calls and triage them as needed.*

### **Project**

We're part of a research project aimed at understanding if Twitter can be used to better connect patients with clinical research opportunities.

We're reaching out to you as part of a research project trying to understand if Twitter can be used to better connect patients with clinical research opportunities.

### **Clinical trials**

It's your involvement that helps researchers to uncover better ways to prevent, diagnose, & treat diseases. Participation is always voluntary and your choice.

Clinical trials are part of clinical research and at the heart of all medical advances. Participation is always voluntary and your choice.

Clinical trials look at new ways to prevent, detect, or treat disease. Participation is your choice and always voluntary.

The goal of clinical trials is to determine if a new test or treatment works and is safe. Participation is your choice and always voluntary.

People participate in clinical trials for a variety of reasons. Participation is your choice and always voluntary.

Clinical trials offer the possibility to have the additional care and attention from the clinical trial staff. Participation is your choice and always voluntary.

